In subjects in the chronic phase after stroke, the effect size of RPSS to improve upper limb motor function is similar to or greater than the effect sizes of other neuromodulation interventions (6). On the other hand, information about the effects of RPSS in the subacute phase after stroke is limited. While all studies in chronic subjects with mild-to-moderate upper limb motor impairments showed benefits of this intervention, only two addressed effects in the subacute stage: one reported an increase in thumb strength after one session of RPSS compared to stimulation to the level of perception (19), whereas another described more significant improvement after *subsensory* RPSS compared to *suprasensory* RPSS (20). In patients in the chronic phase after stroke, suprasensory stimulation led to greater improvements than subsensory stimulation, and the latter was used as a control intervention in patients in the chronic phase after stroke (21, 22). Therefore, the finding of greater effects of subsensory stimulation, compared to suprasensory stimulation in patients in the subacute phase (20), was surprising and raised the hypothesis that optimal intensities/doses of stimulation may be different early, compared to at a later stage after stroke. Until now, patients in the subacute and chronic stages have not been included in a single study, in order to perform head-to-head comparisons between the effects of subsensory and suprasensory stimulation at these two phases after stroke.

Neuronal excitability, activity, or connectivity undergo changes over time after stroke. For instance, motor and sensory representations near the lesion may be remapped after cortical infarcts (23). Connectivity between primary sensorimotor and secondary motor areas changes over several weeks (24). Intracortical inhibition assessed with TMS may decrease in the contralateral motor cortex early after a cerebellar stroke and increase in the chronic phase, more than 6 months later (25).

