### Statistical Analysis

Mean (±SD) or median (ranges) is presented according to the data distribution. Normality is tested with the Shapiro–Wilk test. Changes in JTT scores, strength, GABA levels, and CBF are compared between the four groups with general linear models or generalized estimating equation models with factors INTERVENTION (suprasensory/subsensory) and GROUP (subacute/chronic) according to the distribution of the data. The *p*-values below 0.05 are considered statistically significant.

For perfusion analyses, ratios between CBF in the affected/unaffected hemisphere and ratios between CBF in each region of interest in the affected/unaffected hemisphere are assessed. Due to the exploratory nature of these analyses, corrections for multiple comparisons are not performed.

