For fMRI, a statistical analysis is implemented using a general linear model approach. Activity in ipsilesional and contralesional M1 during finger tapping is modeled by 30 s boxcar convolved with a double gamma function regressor. We also include a regressor with the first temporal derivative of the main regressor and nuisance regressors derived from the extended motion parameters. Two first-level analyses per participant are run, one pre-stimulation and one post-stimulation. Second level of analysis is carried to estimate the within-subject contrast between pre- and post-stimulation using a fixed-effects model, by forcing the random effects to zero in FLAME (FMRIB's Local Analysis of Mixed Effects) (63–65). At the third level of analysis, we estimate contrasts for each group of participants using one-sample *t*-tests to verify if there were effects of stimulation and independent *t*-tests to see changes between groups using a mixed effects model in FLAME (FMRIB's Local Analysis of Mixed Effects) stage 1 (63–65). Z (Gaussianized T/F) statistic images are thresholded using clusters determined by *Z* > 3.1 and a corrected cluster significance threshold of *p* = 0.05 (66). If there is a significant difference in change in motor performance (JTT or strength) between suprasensory and subsensory groups in either the chronic or subacute stage after stroke, bivariate analyses are performed (regressions or chi-square tests) to assess the relationship between each of these variables at baseline, and the magnitude of the improvement in behavior: baseline JTT or strength, age, sex, the intensity of RPSS (relative to sensory threshold), extent of BOLD activation (number of voxels and signal intensity) in M1, CBF (global and regional), or GABA concentration in M1 at baseline. Multiple regression is performed to assess the effects of variables if *p*-values are below 0.1 in bivariate analyses 0.05 (66).

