This study aims to compare the effects of a single session of RPSS on learning and motor performance of patients after stroke in two different stages—chronic and subacute. The results of this study will be critical to help close one of the gaps about effects of RPSS on the performance and motor learning in subjects with stroke. They will be relevant to inform future clinical trials based on mechanisms to tailor RPSS to patients more likely to benefit from this intervention. This goal is achieved by comparing behavioral effects according to time after stroke (primary outcome) and by providing preliminary evidence of mechanisms underlying these effects (secondary outcomes). If there is a relation between time after stroke, GABA levels, BOLD activation or CBF measured with ASL, and responsiveness to RPSS as an add-on treatment to motor training, these factors should be considered to select patients for clinical trials.

One limitation of this study is that only patients with mild-to-moderate upper limb impairments are included. This strategy was adopted because this is a proof-of-principle study and eligibility criteria were narrowed to test a specific hypothesis. More work will be necessary to test whether the effects of RPSS differ according to the time after stroke, in patients with moderate-to-severe upper limb motor impairments.

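### The search for baseline, imaging and GABA predictors of response runs only after a significant mean difference between stimulation types, a condition that says nothing about variation in response

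*Protocol article*

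**What the plan says.** The last part of the protocol article's Statistical Analysis section sets a two-step rule. The opening condition is "If there is a significant difference in change in motor performance (JTT or strength) between suprasensory and subsensory groups", and it is applied phase by phase: "in either the chronic or subacute stage after stroke, bivariate analyses are performed". The purpose of those analyses is "to assess the relationship between each of these variables at baseline, and the magnitude of the improvement in behavior". The listed variables are baseline JTT or strength, age, sex, stimulation intensity relative to sensory threshold, BOLD extent in M1, CBF and GABA. A multiple regression follows for variables with p below 0.1, so it falls under the same condition. No other analysis in the article links these variables to the size of the behavioural change. The significance rule is that p-"values below 0.05 are considered statistically significant".

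The Discussion says that the results should help to "tailor RPSS to patients more likely to benefit from this intervention". It adds that if time after stroke, GABA, BOLD or CBF relate to responsiveness, "these factors should be considered to select patients for clinical trials".

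The INTERVENTION and GROUP models for JTT, strength, GABA and CBF carry no such condition. Nor do the fMRI group contrasts.

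**The concern.** A mean difference between two stimulation types and variation in that difference across patients are separate quantities. Response can depend strongly on a baseline marker while the mean difference is small or zero, and a clear mean difference can be the same in every patient. A significant mean is therefore the wrong trigger for asking which patients respond.

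If the condition is not met, the trial will have collected baseline function, perfusion, BOLD and spectroscopy data, and the plan will not relate them to response. That includes the case of a null average with mixed individual responses, where a predictor analysis would be most informative for selecting patients in later trials.

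**Working it through.** **Inputs.** The Sample Size section gives 68 evaluable patients at 80% power, raised to 72 for 5% dropout, with half in each phase. Allocation is 1:1 (Randomization section). The significance level is 0.05; two-sided is assumed. The SD comes from an earlier study and its value is not given. No effect size is given, so every effect below is an assumption in SD units.

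**The plan's own figure.** 68 / 0.95 = 71.6, rounded up to 72, as stated. The 68 itself cannot be reproduced without the SD and the effect. 72 / 4 = 18 per arm per phase (68 / 4 = 17 evaluable).

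**Chance that JTT meets the condition.** Two-sample t-test with 2n - 2 degrees of freedom and noncentrality d × √(n/2). For n = 18, √(18/2) = 3. The chance in at least one phase, with the same effect in both, is 1 - (1 - p)².

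| d | noncentrality | one phase (p) | at least one phase |
|---|---|---|---|
| 0.3 | 0.9 | 14% | 26% |
| 0.5 | 1.5 | 31% | 52% |
| 0.7 | 2.1 | 53% | 78% |

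With 17 per arm, d = 0.5 gives 29% and 50%.

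**Counting strength.** Pinch or grip can also satisfy the condition. If all three measures had the same effect and correlated at 0.5 (assumed), the chance would be about 79% at d = 0.5 and 95% at d = 0.7. With no effect at all, three independent measures in two phases would satisfy it falsely in 1 - 0.95⁶ = 26% of trials.

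**Responses that cancel within a phase.** Assume a 50/50 baseline marker, with an effect of +0.8 SD in one half and -0.8 SD in the other. The mean difference is zero. By simulation with 18 per arm per phase, JTT meets the condition in at least one phase in about 5% of trials if the marker is exactly balanced in every arm. If the marker falls at random, the figure is about 10%, which matches 1 - 0.95² = 9.75%.

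**The same scenario without the condition.** The treatment-by-marker contrast is 0.8 - (-0.8) = 1.6 SD. With four equal cells its standard error is √(16/N).
- N = 72: standard error 0.471, noncentrality 1.6 / 0.471 = 3.39, power about 92%. Simulations give 90 to 92%.
- N = 48: standard error 0.577, noncentrality 2.77, power about 77% if exactly balanced, and about 74% by simulation if the marker falls at random.

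The 48 matters because the Imaging Outcomes section places MRI at HIAE, and the Sample Size section assigns 48 patients to HIAE or HCFMUSP together. It is an upper bound for imaging markers if no Salvador patients are scanned.

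**Less extreme patterns (17 per arm per phase, random marker).** Chance of a significant interaction on JTT without the condition, and when JTT must satisfy it first:
- +0.8 / -0.8 SD: 89% and 9%
- +0.5 / -0.5 SD: 52% and 5%
- +1.0 / 0 SD: 51% and 22%

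**The case against.** The strongest reply is that the tailoring aim does not rest on this step. The Discussion states "This goal is achieved by comparing behavioral effects according to time after stroke (primary outcome") and through preliminary mechanistic evidence, and neither part is conditional. That stands. A reader might infer that the trial's whole tailoring question could go unanswered; the document does not support that, because time after stroke is always tested.

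A reader might also take the Introduction's report of a subacute result favouring subsensory stimulation, which "was surprising and raised the hypothesis that optimal intensities/doses of stimulation may be different early", as evidence that the condition is likely to fail. It is not. Those opposite directions lie between the phases. The condition is checked within each phase, so they do not cancel and could satisfy it. The harmful case needs opposite responses among patients in the same phase, and the document reports none.

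Two further points stand in part. JTT figures for a single phase understate how often the condition is met, since either phase and either kind of measure suffices. The +0.8/-0.8 pattern is an extreme illustration without a source in the document.

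Finally, confining a predictor search to settings with a demonstrated effect can be defended as caution, given many candidate variables and a p < 0.1 screen. But the condition is poor error control: it can be met by chance, and it does not limit the number of predictors tested afterwards. The plan already treats its perfusion analyses as exploratory and leaves them uncorrected, so an exploratory label would be consistent with it.

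**Conclusion.** The point holds in a limited form. The article fixes a rule under which the only analyses linking baseline function, BOLD, CBF and GABA to improvement depend on a mean difference that does not bear on variation in response. Tailoring by time after stroke and the primary analysis are untouched.

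The loss is a matter of probability. At an assumed 0.5 SD in both phases, the condition would fail on JTT in about 48% of trials (100 - 52), and less often once strength is counted. If effects cancel within a phase on both JTT and strength, it would be met only by chance.

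There is a second weakness. A bivariate regression of improvement on a baseline variable cannot separate response to the type of stimulation from general prognosis, even when the condition is met.

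**What to change.** Delete the condition and run the predictor analyses whatever the main result, labelled exploratory. Replace the bivariate regressions with models containing a treatment-by-baseline-variable term. Report each estimate with its 95% CI, in the patients who have that marker, and state the number. Stimulation intensity relative to sensory threshold is set by arm, so analyse it separately (for example within arm) and not as a baseline interaction.

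No new data are needed. The cost is more than a deleted clause: the model form changes, and exploratory results will also be reported after a null main result. Imaging interactions will be imprecise, so they should be read as estimates for planning and not as tests.

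### The predictor analysis relates improvement to baseline variables with no treatment-by-variable term, so it shows who improves, not who responds to RPSS

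*Protocol article*

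**What the plan says.** The last part of the Statistical Analysis section has a two-step search for predictors.

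- **Trigger.** It runs only on this condition: "If there is a significant difference in change in motor performance (JTT or strength) between suprasensory and subsensory groups", in either phase.
- **Step 1.** Then "bivariate analyses are performed (regressions or chi-square tests) to assess the relationship between each of these variables at baseline". What each variable is related to is how much the patient improved. The variables listed are JTT or strength before stimulation, age, sex, stimulation intensity as a multiple of threshold, M1 BOLD activation, CBF and GABA.
- **Step 2.** "Multiple regression is performed to assess the effects of variables" whose p-values "are below 0.1 in bivariate analyses".

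Neither step states a treatment term or a treatment-by-variable term. The patients analysed (both arms, or suprasensory only) are not named. The main model in the same section has INTERVENTION and GROUP as factors, but these predictors are not in it.

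The Primary Outcome section defines JTT change as a percentage of pre-stimulation JTT. The Discussion says that if time after stroke, GABA, BOLD or CBF is related to responsiveness to RPSS, these factors should be considered in selecting patients for trials. It gives as the study's purpose to help "tailor RPSS to patients more likely to benefit from this intervention".

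**The concern.** Responsiveness to RPSS is a contrast: does the suprasensory-minus-subsensory difference vary with the marker? Improvement is not that contrast. Under Interventions, both arms are familiarised with the JTT, tested, retested after stimulation, trained for two blocks and tested again, so practice gains common to both arms are part of each patient's improvement. A variable that predicts those gains will correlate with improvement even if it has no bearing on the RPSS effect. Conversely, a marker that works in opposite directions in the two arms can cancel out when they are pooled.

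Two listed predictors have a further problem. Baseline JTT is both the starting value and the denominator of the JTT change. RPSS intensity relative to threshold is fixed by arm and adjusted during the two hours of stimulation, so it is not a baseline characteristic.

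At stake is the choice of markers for later trials: wrong ones could be carried forward and right ones missed.

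**Working it through.** **Inputs from the protocol.** 72 patients: 68 allowing for 5% dropout, 68/0.95 = 71.6, so 72, which reproduces. Allocation 1:1. Imaging outcomes are assessed at HIAE only, and 48 patients come from HIAE or HCFMUSP, so at most 48 have imaging. Screen at p < 0.1. The protocol gives neither the effect size nor the SD behind the 68.

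**Assumptions.** Two-sided tests. Treatment effect d = 0.67, close to what 34 v 34 detects with 80% power: (1.960 + 0.842) × √(2/34) = 0.68. Prognostic correlation of the marker with improvement 0.3 to 0.5, equal in both arms, so the true interaction is zero. 20,000 simulated trials per setting.

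**1. Prognostic marker, no effect modification: proportion with p < 0.1**

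| Patients | Both arms pooled | Suprasensory only | Treatment × marker |
|---|---|---|---|
| 72 | 79% to 99.6% | 56% to 94% | about 10% |
| 48 | 64% to 97% | 43% to 83% | about 10% |
| 36 (one phase) | 52% to 92% | 34% to 71% | about 10% |

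Hand check of the first cell. The treatment difference adds 0.67²/4 = 0.112 to the within-arm variance of 1, so the pooled correlation is 0.3/√1.112 = 0.284. Fisher's z is 0.293; times √(72 − 3) = 8.31 gives 2.43. Then Φ(2.43 − 1.645) = 78%. For 0.5: 0.474, z = 0.515, product 4.28, Φ(2.64) = 99.6%.

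**2. True modifier with opposite slopes (assumed +0.4 and −0.4).** The pooled screen finds it in about 12.5% of trials. The interaction test finds it in 87% (48 patients) to 97% (72 patients).

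**3. Baseline JTT against percent change.** The printed formula lacks inner brackets; I read it as (pre − post)/pre × 100. On the log scale, let the true value have variance s² and each test independent error variance e². With no treatment effect, cov(log pre, log pre − log post) = e², var(log pre) = s² + e², and var(difference) = 2e². Hence

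r = e²/√[(s² + e²) × 2e²] = √[(1 − ICC)/2].

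The simulation on the percent scale assumed a between-patient CV of 0.5 and a constant proportional effect of 10% v 0%, unrelated to baseline:

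| Assumed ICC | r, log-scale formula | Mean r, percent scale | p < 0.1 at N = 72 |
|---|---|---|---|
| 0.99 | 0.07 | 0.05 | 13% |
| 0.95 | 0.16 | 0.14 | 32% |
| 0.90 | 0.22 | 0.20 | 54% |
| 0.80 | 0.32 | 0.28 | 81% |

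The nominal rate is 10%. The treatment-by-baseline test stays at about 10% throughout.

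**4. RPSS intensity.** Assumed uniform at 0.5 to 0.95 times threshold in the subsensory arm and 1.2 to 3 times in the suprasensory arm, with no dose effect within arm. With arms pooled (N = 72) it passes p < 0.1 in 79% of trials; in the suprasensory arm alone, in about 10%.

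**The case against.** The best defence is that this is a conditional follow-up in a proof-of-principle trial, that multiple regression does not exclude INTERVENTION as a covariate, and that an article may leave details to the full protocol or analysis plan. It stands in part: the primary comparison is untouched, and the population analysed could well be specified elsewhere. It does not remove the main point. The method is stated, and a treatment main effect is not an interaction. Restricting to suprasensory patients does not help, as the first table shows. The trigger decides only whether the analysis runs, not what it estimates.

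Several stronger readings are tempting but not supported.

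- *A reader might infer that slow baseline JTT will very probably be reported as a marker whether or not RPSS works.* The trigger limits this. If six tests are assumed (JTT, pinch and grip in two phases) and independent, it opens falsely in 1 − 0.95⁶ = 26.5% of trials with no effect. With the trigger included, and assuming a true log-JTT SD of 0.4 and error SD of 0.10 to 0.25, baseline JTT is both triggered and passes the screen in 7% to 18% of null trials with 36 patients and 11% to 25% with 72.
- *That patient selection would rest on these artefacts.* The Discussion's list for selection does not include baseline JTT or RPSS intensity. It says the tailoring goal is met by comparing behavioural effects by time after stroke, with mechanistic evidence as preliminary support. The missing interaction still affects GABA, BOLD and CBF, which are on that list.
- *That intensity merely restates allocation.* This holds only if arms are pooled, which the protocol does not say.
- *That ten predictors screened at 0.1 give a 65% chance of a false finding.* 1 − 0.9¹⁰ = 65% assumes ten independent predictors and counts entry into a regression, not a declared result.

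**Conclusion.** The point holds as a mismatch between a stated method and the use made of it. Regressing improvement on a marker does not estimate modification of the RPSS effect, whichever patients are used. That conclusion needs no numerical assumption. The error rates depend on the assumed prognostic correlation of 0.3 to 0.5.

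The JTT coupling is algebraically certain, but its size is unknown because the documents give no test-retest error: negligible near an ICC of 0.99, material at 0.80 or below. It is shown for JTT only, since no formula for strength change is given. The intensity problem is conditional on pooling. This should be corrected, but it concerns an exploratory analysis and does not threaten the primary result.

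**What to change.** For each marker, fit the outcome on INTERVENTION, marker and INTERVENTION × marker, plus GROUP, in both randomised arms. Report the interaction with its 95% CI, labelled exploratory. For JTT, model log post-stimulation JTT adjusted for log pre-stimulation JTT; baseline JTT as a modifier is then INTERVENTION × log pre-stimulation JTT. Examine RPSS intensity only within the suprasensory arm, and do not call it a baseline variable.

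If the present analysis is kept, describe its results as predictors of improvement and remove the reading as responsiveness. The significance trigger may stay; whether to keep it, the chi-square tests or the 0.1 screen is a matter of preference.

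The cost is wording only, with no new data. The price is precision: for a marker in SD units, the 95% half-width of the interaction is about 1.96 × √(4/72) = 0.46 residual SDs with 72 patients and 1.96 × √(4/48) = 0.57 with 48, the most that imaging can supply. Claims for later trials will have to be correspondingly modest.

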### Interventions

Suprasensory or subsensory RPSS was initially administered in the second experimental session (Figure 1) at HSR and at HIAE, and also in the third experimental session at HIAE. After approval of an amendment in August 2021, RPSS started to be administered in the first visit, after the assessment of the patient characteristics. This protocol corresponds to version 5 of the project and includes all the amendments approved until August 2021.

Subjects are comfortably seated during RPSS. Trains of electrical pulses (1 ms of duration for each) at a frequency of 10 Hz are delivered at 1 Hz (500 ms on and 500 ms off) to the median nerve on the wrist by one pair of surface electrodes (Kendall; cathode, proximal) connected to a customized stimulator (Alfamedic Ltda, São Paulo, Brazil; maximum output, 130 V). The median nerve is stimulated between the tendons of the flexor carpi radialis and palmaris longus with the cathode positioned 2–3 cm proximal to the wrist. Three measurements of the minimum stimulation intensity required to elicit paresthesia (sensory threshold) are performed.

For suprasensory stimulation, intensities are set at the highest intensity able to induce paresthesia without overt muscle contraction or pain and adjusted if required (21, 39, 45). In subsensory, the intensity of stimulation is below sensory threshold, not sufficient to elicit paresthesia (20).

Every 5 min, participants are asked about the sensations elicited by stimulation in order to avoid fluctuations in wakefulness and in attention to the stimulated body part (46). The intensity of stimulation is increased if paresthesia becomes weaker, and lowered if they become uncomfortable or during the 2-h period. Usually, it is necessary to adjust the intensity of stimulation due to changes in the intensity of paresthesia during the 2-h period. There may be changes in skin impedance and subjects in the RPSS group may report increase or decrease in paresthesia. The intensity of stimulation is then adjusted to elicit strong paresthesia in the absence of pain or movement. In the subsensory group, the initial intensity defined so that no sensations are elicited may lead to paresthesia during the 2-h period. When this occurs, the intensity of stimulation is lowered below the sensory threshold. During RPSS, subjects watch videos of their choice.

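### RPSS intensity relative to sensory threshold is treated as a baseline predictor, but the allocated arm sets it; if the arms are pooled without an arm term, it is close to a proxy for treatment

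*Protocol article*

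**What the plan says.** In the protocol article, Statistical Analysis, a secondary analysis of correlates is opened by this condition: "significant difference in change in motor performance (JTT or strength) between suprasensory and subsensory groups in either the chronic or subacute stage after stroke". After that, bivariate regressions or chi-square tests are run "to assess the relationship between each of these variables at baseline, and the magnitude of the improvement in behavior". The list contains baseline JTT or strength, age, sex, imaging measures and GABA, and with them "the intensity of RPSS (relative to sensory threshold), extent of BOLD activation (number of voxels and signal intensity) in M1". A variable goes forward to multiple regression if its "values are below 0.1 in bivariate analyses". Treatment arm is not among the listed variables, and no restriction to one arm is stated.

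The Interventions section defines the intensity. For suprasensory stimulation, "intensities are set at the highest intensity able to induce paresthesia without overt muscle contraction or pain and adjusted if required". For the other arm: "In subsensory, the intensity of stimulation is below sensory threshold, not sufficient to elicit paresthesia". Patients are asked about sensations every 5 min, and "Usually, it is necessary to adjust the intensity of stimulation due to changes in the intensity of paresthesia during the 2-h period".

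**The concern.** Two things do not fit together.

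- **The label.** A quantity chosen according to the allocated arm, and then changed during treatment in response to what the patient reports, is not a baseline variable. Age, sex and baseline JTT are.
- **The overlap.** By the article's own definitions the ratio of intensity to threshold lies below 1 in every subsensory patient and above 1 in every suprasensory patient. In a two-variable regression across both arms, the slope on intensity mostly carries the arm difference, which is the result that opened the analysis.

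The Introduction raises the possibility that the best intensity differs by phase, and the Discussion says the results will help tailor RPSS. A reader could take a pooled slope as evidence that, among patients given suprasensory stimulation, intensity matters. The pooled slope cannot show that.

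**Working it through.** **Inputs from the article.** 68 evaluable patients at 80% power, 5% dropout, 72 enrolled, half in each phase (Sample Size); 1:1 allocation (Randomization); trigger in either phase and carry-forward at p<0.1 (Statistical Analysis). For significance, "values below 0.05 are considered statistically significant"; two-sided testing is assumed.

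**Stated figure.** 68/0.95 = 71.6, rounded up to 72, so the enrolled number reproduces. The 68 itself cannot be re-derived because no effect or SD is given. Four equal cells give 68/4 = 17 evaluable per cell. By the normal approximation, the detectable difference is (1.96 + 0.84) × √(2/n): 0.96 SD with n = 17 per arm and 0.68 SD with n = 34 per arm. This motivates the effect sizes used below.

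**Why a pooled regression echoes the arm difference.** If intensity has no relation to improvement within either arm, then approximately

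r(improvement, intensity) = r(intensity, arm) × r(improvement, arm).

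Within one phase there are 34 patients and 32 degrees of freedom. Using r = t/√(t² + 32):

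- The trigger at p<0.05 needs r(improvement, arm) of at least 2.037/√(2.037² + 32) = 0.339.
- Carry-forward at p<0.1 needs r(improvement, intensity) of at least 1.694/√(1.694² + 32) = 0.287.
- In a trial that only just triggers, the expected correlation with intensity is 0.92 × 0.339 = 0.312 if r(intensity, arm) is 0.92, and 0.80 × 0.339 = 0.271 if it is 0.80.

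So even the weakest triggering result puts intensity at or near the carry-forward limit.

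**Simulation.** 6,000 trials per scenario, 17 per cell, normal outcome, one endpoint, no within-arm relation. The article gives no intensity values, so the ratios are assumptions: uniform 0.70-0.95 in the subsensory arm; normal with mean/SD 1.8/0.3 or 2.2/0.8 (also 1.3/0.1 and 3.0/1.5), truncated at 1.05, in the suprasensory arm. The correlation of intensity with arm was then 0.76-0.94. Trigger: t-test p<0.05 in either phase. Shares are of triggered trials, for effects of 0.7-0.97 SD unless stated.

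| Analysis of intensity | p<0.1 | p<0.05 |
|---|---|---|
| Arms pooled within the triggering phase | 75-97% | 59-92% |
| Four groups pooled, same effect in both phases | 85-99% | 74-97% |
| Four groups pooled, effect in one phase only | 44-64% | 31-50% |
| Four groups pooled, opposite effects by phase | 6-11% | not above 6% |
| Arm added to the pooled model | 8-15% | 4-9% |
| Suprasensory arm only | 7-11% | 4-6% |

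Within the triggering phase, an effect of 0.5 SD gives 69-87% at p<0.1. A false-positive trigger (no true effect in either phase) still gives 66-85%.

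**The case against.** The strongest objection is that the article never says the arms are pooled. It speaks in the Discussion of responsiveness to RPSS, and in one place in Interventions sets the RPSS group against the subsensory group. A regression within the suprasensory arm is therefore an open reading, and under it the error rate is about nominal. The analysis set for an exploratory regression is also a detail that an article may leave to the analysis plan. This stands in part: pooling cannot be asserted as the plan. But a bivariate analysis has no arm term, no restriction to one arm is stated, and the baseline label, which the article does state, conflicts with its own Interventions section whatever is pooled.

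A second objection is that the randomised comparison of the two stimulation levels in the two phases, not this regression, answers the question about intensity and phase. That is right. A pooled slope would partly restate a real randomised contrast. It would be redundant with that contrast, and misleading only if read as a gradient beyond it.

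Two stronger readings are tempting, and neither is supported. One is that a dose-response will appear almost whenever the arms differ. That depends on the unstated pooling: the share is about half when four groups are pooled and only one phase has an effect, and with opposite effects, a possibility that fits the Introduction, pooling hides the association. The trigger also has no direction, so if subsensory stimulation does better the slope changes sign. The other is that no model can help because no intensity occurs in both arms. A model with arm, intensity and their product gives the separate within-arm slopes, which need no overlap.

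**Conclusion.** The point holds in a limited form. Intensity relative to threshold is wrongly grouped with baseline variables: it is fixed by allocation and adjusted after randomisation. If the arms are pooled without an arm term, it is close to a proxy for treatment. Depending on how the phases are combined, the same analysis can then give a spurious gradient in most triggered trials, give one in roughly half, or mask an association.

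The percentages rest on assumed intensity ratios, assumed standardised effects, one endpoint and a normal outcome. The direction of the argument does not, since the separation of the arms follows from the definitions under Interventions. This is a cheap improvement to an exploratory analysis. It does not touch the primary outcome, its test or the sample size.

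**What to change.** 1. Take RPSS intensity out of the pooled list of baseline predictors.
2. Analyse it within the suprasensory arm, or in a model containing arm, phase, their interaction and a separate intensity slope for each arm. Arm alone as a covariate gives 8-15% at p<0.1; the upper end arises when the phases have opposite effects and the arm-by-phase term is left out.
3. State which intensity is used. One option is the initial intensity over the initial threshold, with the average delivered over the 2 h as a sensitivity analysis. The delivered average is more strongly driven by patient response, and so is better kept as the secondary version.
4. Label the analysis exploratory and the variable post-randomisation.

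The cost is a few sentences of analysis text and, if not already recorded, entry of the adjusted intensities. Within-arm slopes rest on about half the patients (34 in the suprasensory arm over both phases, 17 in one phase), so a real relation would be estimated less precisely.
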